Acupuncture has been used worldwide to treat various conditions and diseases. In the context of clinical practice in Korea, acupuncture is one of the most frequently delivered modalities of medical treatment. In 1997, an NIH conference reached the consensus that acupuncture could be employed as a useful part of treatments in several clinical situations [16]. Since then, acupuncture has been increasingly adapted to treat a wide range of conditions and numerous related research efforts are currently being conducted around the globe. According to recent studies on the safety of acupuncture, it represents one of the safer forms of medical intervention with a low rate of adverse effects if performed by well-trained practitioners [17-19]. For treatment of hot flushes, acupuncture causes only minor side effects as opposed to conservative therapies, including HRT and non-hormonal agents, which cause more drastic adverse effects [8-11,13,17-19].

To date, acupuncture treatments have been increasingly utilized in several clinical trials for hot flushes due to menopause, breast cancer, and prostate cancer in males. Two randomized controlled trials (RCTs) (n = 24, n = 30) were carried out comparing electroacupuncture to sham acupuncture. These trials showed no significant differences between the two groups, but they did show considerable symptom reductions within each group [20,21]. One relatively large RCT (n = 103) showed no significant differences between real acupuncture and sham acupuncture [22], but a small RCT (n = 29) found that there was a significant difference between active acupuncture and placebo needles in terms of the severity, but not the frequency, of nocturnal hot flushes [23].

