### Interventions

TKA regimens designed according to TKM clinical experts will be used in this trial for alleviating hot flushes and vasomotor symptoms by balancing yin and yang in the participant. These regimens were also used in two previous studies [25], one of which is unpublished and mentioned above. The TKM doctors who conduct the treatments have practiced for at least 3 years in the clinic; they belong to each clinical center spread among different provinces in South Korea.

Participants will be randomly assigned to either the acupuncture treatment plus usual care group or the usual care alone group. The acupuncture treatment plus usual care group will receive acupuncture 3 times/week, for a total of 12 sessions. Six acupuncture points (ST36, SP6, LI4, PC6, HT7, HT8) will be inserted bilaterally in the four peripheral extremes and one point (CV4) will be inserted unilaterally in the lower abdominal region. TKM doctors will manually manipulate the acupuncture needles with de-qi sensation and maintain the needles for 20 minutes with intermittent manual stimulation. Infrared irradiation will be used to warm the lower abdomen during the 20 minutes of acupuncture treatment, as it is performed in conjunction with acupuncture, generally.

TKM doctors will use sterile, disposable needles with a length of 40 mm and a diameter of 0.25 mm (Dongbang Acupuncture Inc, Korea). They will be inserted to a depth of 3–15 mm, according to the points selected.

Participants who will be allocated to usual care alone group will receive no acupuncture treatments throughout the 4 weeks. They will record their hot flush symptoms in a daily diary. After four weeks, if participants elect to try the acupuncture treatment, the same treatment will be provided.

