### Statistical methods and sample size

Analyses will be performed for two populations: 1) an intention-to-treat population consisting of all randomized participants with at least one measurable outcome report following acupuncture treatment (missing data will be replaced with last observation values); 2) a per protocol population including only participants without major protocol deviations. All data will be analyzed descriptively. All main analyses will be based on the intention-to-treat population. For primary and secondary outcome measures, the mean differences from baseline values to the end of treatment will be compared using two-sample t-test or Wilcoxon rank sum test. A trend test will also be performed using repeated measures analysis of variance. We adjusted for possible confounders using criteria of statistical significance.

All adverse events reported during the study will be included in the charts; then incidences of adverse events will be calculated. The percentage of the subjects with adverse events in each group will be calculated and compared with the chi-squared test or Fisher's exact test value.

Statistical analyses will be performed using the SAS statistical package program (ver. 9.1.3) and the level of significance will be established at α < 0.05. In calculating the sample size, we assumed a power of 90% and α value of 5%, in order to detect a hot flush score difference of 15.34 with a standard deviation of 26.5 drawn by two previous studies in Korea [24,41]. Therefore the acupuncture plus usual care and usual care alone group (2:1 allocation) will include 120 and 60 participants, respectively, allowing for a 20% withdrawal rate. This implies a sample size of 45 for each center, with 30 participants per acupuncture treatment plus usual care group and 15 per usual care alone group.

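### The between-arm adverse event comparison counts all reported events, not only those from the weekly collection common to both arms, and names only a significance test

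*Protocol article*

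**What the plan says.** All places are in the Methods of the protocol article.

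- **Statistical methods and sample size** sets what is counted: "All adverse events reported during the study will be included in the charts; then incidences of adverse events will be calculated". It then sets the comparison: "The percentage of the subjects with adverse events in each group will be calculated and compared with the chi-squared test" or Fisher's test. No interval estimate is named for it.
- **Interventions** gives the contact pattern. The acupuncture arm "will receive acupuncture 3 times/week, for a total of 12 sessions" over four weeks. The usual care arm "will receive no acupuncture treatments throughout the 4 weeks".
- **Study outcome, Table 2** marks adverse effects at weeks 1, 2, 3 and 4, in one schedule that is not split by arm. The text message and telephone reminders go to both arms and concern the diary.
- **Data and safety monitoring** rests the safety assessment mainly on event frequencies, with counts and percentages, a split by body system, and severity or relatedness listed.
- The trial is unblinded. Study outcome concedes that some bias from this may remain.

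**The concern.** Two features of the stated comparison limit what it can show.

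First, the count is wider than the common schedule. Women in the acupuncture arm meet a practitioner 12 times in four weeks and can mention a headache or a poor night each time. Women on usual care have no matching occasion. Since the rule takes every reported event, background complaints can be recorded more fully in one arm, and the difference in percentages then mixes harm with opportunity to report.

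Second, the only between-arm inference named is a p-value. The trial is sized for the hot flush score, and the Background expects few harms, saying of acupuncture that "it represents one of the safer forms of medical intervention with a low rate of adverse effects". With rare events, a non-significant test says little.

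Both matter because lower harm than hormone therapy is one of the Background's arguments for acupuncture.

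**Working it through.** **Plan's own sample size.** Inputs from Statistical methods and sample size: difference 15.34, SD 26.5, power 90%, α 5% (taken as two-sided), 2:1 allocation, 20% withdrawal.

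Control n = (1 + 1/2) × (1.960 + 1.282)² × 26.5² / 15.34² = 47.04, rounded up to 48, so 96 in the acupuncture arm. Dividing by 0.80 gives 60 and 120, as stated. No adverse event rate, power or margin is given, so every event rate below is an assumption.

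**Extra contacts.** Assume that 20% of women in both arms have a background complaint lasting the four weeks, that there is no true harm, and that each contact brings the complaint out independently with probability q. There are 12 contacts in the acupuncture arm and 4 weekly points in the control arm. The recorded percentage is 20% × [1 − (1 − q)^k], with k = 12 or 4. False rejection is the exact probability of two-sided Fisher p < 0.05, summed over all 2×2 tables for 120 versus 60.

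| q | captured, 12 contacts | captured, 4 contacts | ratio | recorded % | Fisher rejects |
|---|---|---|---|---|---|
| 0.2 | 0.931 | 0.590 | 1.58 | 18.6 vs 11.8 | about 17% |
| 0.3 | 0.986 | 0.760 | 1.30 | 19.7 vs 15.2 | about 9% |
| 0.5 | 1.000 | 0.938 | 1.07 | 20.0 vs 18.8 | about 4% |
| no bias | – | – | 1.00 | 20 vs 20 | 3.9% |

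The same question can be put without a contact model. With a true 20% in both arms and full capture in the acupuncture arm, control capture of 90%, 75% or 50% gives false rejection of 4.7%, 10% or 36%.

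**Power for uncommon harms.** Exact power of Fisher's test (two-sided 5%), acupuncture versus control, rates assumed:

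| rates | 120 vs 60 | 96 vs 48 (after 20% withdrawal) |
|---|---|---|
| 5% vs 0% | 15% | 5% |
| 10% vs 5% | 14% | 10% |
| 10% vs 3% | 31% | – |
| 20% vs 10% | 36% | 30% |

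The uncorrected chi-squared test does somewhat better (18.5% for 10% versus 5%, 40% for 20% versus 10%, at 120 versus 60), but the picture is the same.

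**Worked example.** With 8/120 (6.7%) versus 0/60, Fisher p = 0.053. With 9/120 versus 0/60, p = 0.030. For 8 versus 0, the Wilson limits are 3.4% to 12.6% and 0% to 6.0%. Newcombe's interval for the difference is therefore:

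- lower: 6.67 − √[(6.67 − 3.42)² + 6.02²] = −0.2 points
- upper: 6.67 + (12.61 − 6.67) = 12.6 points

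The p-value alone would read as no difference. The interval shows that an excess of up to 12.6 points remains compatible with the data.

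**The case against.** The case against is substantial.

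- **Safety does not hang on the test.** A reader might infer from the statistical section that the test is the safety verdict. Data and safety monitoring rests safety mainly on descriptive frequencies, and nothing says that a non-significant result means equal safety. This stands. What remains is that the test is the only between-arm safety inference named.
- **Unequal asking is not documented.** Table 2 gives both arms the same weekly collection, and nothing says that events are solicited at needling sessions. This also stands: unequal capture is an inference from the extra contacts and the all-events rule. The exact question may be in the full protocol or the case report form, but the rule on what is counted is stated here and is wider than the schedule.
- **The bias may be small.** A reader might take three contacts a week against one and, at q = 0.3, infer 2.2-fold capture (0.657/0.30). That describes one week, and so only complaints confined to about a week. The endpoint is per woman over the study, and for a persistent complaint the ratio is 1.30. From q = 0.5 upwards the effect nearly disappears.
- **Low power for uncommon events is common to trials sized on efficacy.** True, and no stated figure is wrong. It is a reason to report an interval, not a flaw in the sample size.
- **Events caused by needling are a real treatment difference, not an artefact.** Agreed. The fix keeps them visible.

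**Conclusion.** The point holds as an inexpensive improvement to the stated analysis. The comparison is open to unequal ascertainment because it counts all reported events in an unblinded trial with 12 treatment sessions in one arm and none in the other.

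The documents do not allow the size of this bias to be fixed. Under the persistent-complaint model it runs from negligible (q = 0.5 or more) to a false rejection rate of about 17% (q = 0.2). Both q and the 20% background rate are assumptions.

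The power point needs no assumption about reporting, only that harms are uncommon: about 31% for 10% versus 3%, and about 15% or less for 5% versus 0% or 10% versus 5%. A non-significant p-value would not support a statement of similar safety.

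The documents do not support saying that safety is decided by the test, or that capture is known to differ between arms.

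**What to change.** In Statistical methods and sample size:

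1. Base the between-arm comparison on events collected at the weekly points already in Table 2 (weeks 1 to 4), with the same question in both arms.
2. Tabulate events noted at needling sessions separately, without a between-arm test. Keep the all-events table as description.
3. Report the risk difference with a 95% confidence interval as the main between-arm safety result, instead of relying on the p-value.

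Restricting the comparison to weeks 1 to 4 also keeps out events in control women who take up the acupuncture offered after four weeks.

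The cost is one case report form question, one sentence of analysis text and one more table, with no added visits. The downside is that session-noted events are described but not compared. A needling effect that a woman reports again at the weekly question stays in the comparison. The change equalises the opportunity to report. It does not remove the influence of knowing the allocation, and it does not raise power, but the interval shows how much remains uncertain.

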### Data handling

Investigators will enter the information required by the protocol into the Case Report Forms (CRFs). Non-obvious errors or omissions are entered on data query forms, which will be returned to the investigational site for resolution.

The data from all centres are pooled and summarized with respect to demographic baseline characteristics, effectiveness and safety observations.

### Data and safety monitoring

Regular monitoring will be conducted for quality control. Also, investigators can be convened to discuss practical issues that may be encountered such as adjusting recruitment capacity within each center, dealing with serious adverse events, revising the protocol, as well as certain important issues that may be raised by investigators and participants.

The assessment of safety will be based mainly on the frequency of adverse events, which includes all serious adverse events. Information regarding adverse events will be summarized by presenting the number and percentage of participants experiencing any adverse event, with the information also divided by body system. Any other information collected (e.g. severity or relatedness to acupuncture treatments) will be listed as appropriate.

## Abbreviations

HRT: Hormone Replacement Therapy; CAM: Complementary and Alternative Medicine; TKA: Traditional Korean Acupuncture; MRS: Menopause Rating Scale; NIH: National Institutes of Health; RCT: Randomized Controlled Trial; TSH: Thyroid Stimulating Hormone; FSH: Follicle Stimulating Hormone; SSRI: Selective Serotonin Reuptake Inhibitor; OTC: Over The Counter; TKM: Traditional Korean Medicine; SMS: Short Message Service; CRF: Case Report Form.
